#### Primary outcome

The scientific rationale is that the establishment of return-to-work (RTW) experts for inpatient mental health patients focuses on the workplace needs of these patients, leading to a better usage of existing resources as part of a work-related discharge management, and thus to a more successful return to the workplace.

The primary objective is to display this improved return to the workplace after in-patient psychiatric care as a group difference (intervention vs. control) using days in work and days of incapacity to work during 1 year after discharge from hospital.

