### Sample size calculation and statistical analysis

The aim is to obtain a sample of *n* = 28 clusters (i.e. psychiatric acute wards) with a total of 200 patients (8–10 per cluster). For this, about 2000 patients need to be screened (Mernyi et al., 2018).

In order to be able to demonstrate a significant result with a power of 80% assuming a small to medium effect size (0.5), a total sample size of 128 patients is required (two-sided independent samples t-test, α = 0.05). With regard to expected drop-outs (drop-out rate 30–40%), this minimum number of cases is planned to be exceeded by 72 patients. Thus, a total of 200 patients are to be included (100 in each group).

The primary analysis will be a comparison of days in work at T4 between the intervention and control groups. To assess the effect of the intervention on the continuous primary outcome, a random effects linear regression model will be fitted with ward (cluster) as a random effect term and intervention group as a fixed effect. The point estimate for the intervention effect will be reported together with the corresponding 95% confidence interval. A *p*-value < 0.05 will be considered as providing statistical significant evidence of a group difference. A per protocol approach will be taken to the analysis, i.e. patients in intervention clusters will be analyzed in this group, if they had contact with the RTW-expert at least once during their inpatient stay and once after discharge.

Exploratory analyses will be performed to assess the effect of the intervention on the secondary outcome measures. Random effect linear models will be fitted to the continuous secondary outcome measures, analogous to the primary analysis. For binary secondary outcome measures, logistic regression models using GEEs will be fitted.

The health economic analysis is based on the net benefit approach. To analyze the cost-effectiveness of the RWT intervention, the incremental cost-effectiveness ratio (ICER) is determined for gaining a QALY compared to routine treatment. The estimation of ICER stochastic uncertainty is done by nonparametric bootstrapping and the determination of the cost-effectiveness acceptance curve [29].

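### The one-value-per-patient T4 model has no place for the T2 and T3 work-day reports of patients lost later, which costs precision and leaves the comparison open to bias if loss depends on work differently by arm

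*Protocol article*

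**What the plan says.** All references are to the protocol article.

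- *Sample size calculation and statistical analysis* fixes the time point, "The primary analysis will be a comparison of days in work at T4 between the intervention and control groups", and the model: "a random effects linear regression model will be fitted with ward (cluster) as a random effect term and intervention group as a fixed effect". There is no visit term and no patient-level term.
- The same section gives the sample size as "power of 80% assuming a small to medium effect size (0.5), a total sample size of 128 patients is required". The calculation behind that figure is named there as well: "two-sided independent samples t-test, α = 0.05". Loss to follow-up is handled by recruitment: "With regard to expected drop-outs (drop-out rate 30–40%), this minimum number of cases is planned to be exceeded by 72 patients". The total follows: "Thus, a total of 200 patients are to be included (100 in each group").
- *Primary outcome* sets the objective over a full year, "using days in work and days of incapacity to work during 1 year after discharge from hospital".
- *Data collection*, Table 1, marks days at work at T2 (3 months), T3 (6 months) and T4 (12 months after release).
- The analysis set is stated in the statistical section: "A per protocol approach will be taken to the analysis". In the intervention arm this requires one inpatient and one post-discharge contact.

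**The concern.** The outcome describes a year and is asked about three times, but the model takes only a T4 value. By the plan's own expectation, 60 to 80 of 200 patients will have no T4 value. Some of them will already have reported their work days at 3 or 6 months, and those reports bear directly on the year's outcome.

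Two things are at stake. The first is precision: observed outcome information is left unused whatever the reason for loss. The second is bias: people who are not working may be harder to keep in follow-up, and this link could differ by arm, because intervention patients have access to a return-to-work expert for up to half a year and control patients do not. The article gives no data on whether loss behaves this way.

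**Working it through.** **1. The plan's own figures.** A two-sided t-test with d = 0.5, α = 0.05 and power 80% needs 63.77 per arm, so 64 per arm, or 128. Then 128/(1 − 0.36) = 200, and 72/200 = 36%. The plan's figures reproduce, and the arithmetic counts drop-outs as not analysed.

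**2. Power as planned.** With N patients analysed, power ≈ Φ(0.5·√(N/4) − 1.96). Ward clustering is ignored, as in the plan's calculation, so these powers serve only for comparison with one another.

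- 30% loss: N = 140, power 84%.
- 36% loss: N = 128, power 81% (80% by the exact t-test).
- 40% loss: N = 120, power 78%.

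**3. Precision recovered from T2 and T3.** Assumptions, none of them in the article:

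- the three reports are interval counts covering 3, 3 and 6 months (weights 0.25, 0.25, 0.5);
- the intervals have equal variance and a common correlation ρ of 0.5, 0.7 or 0.85;
- a share s of drop-outs gave both T2 and T3, and the rest add nothing;
- loss is unrelated to outcome.

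For loss d, put r = 1 − d and r₃ = 1 − d + d·s. The variance of the year total is V = 0.375 + 0.625ρ, and the residual variance of the last interval given the first two is R = 1 − 2ρ²/(1 + ρ). Then

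v = V/r₃ + (1/r − 1/r₃)·0.25·R, and effective N = 200·V/v.

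Example with ρ = 0.7, d = 0.36, s = 0.5:

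- V = 0.8125, R = 0.4235, r = 0.64, r₃ = 0.82;
- v = 0.9909 + 0.3430 × 0.25 × 0.4235 = 1.0272;
- effective N = 162.5/1.0272 = 158, power 88%.

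| Share of drop-outs with T2 and T3 | Effective N at 36% loss (T4 only: 128) | Power (T4 only: 80.7%) |
|---|---|---|
| all | 176–193 | 91.3–93.5% |
| half | 154–161 | 87.2–88.8% |
| a quarter | 141–145 | 84.4–85.3% |

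The gain runs from 84.4 − 80.7 = 3.7 points to 93.5 − 80.7 = 12.8 points. At 40% loss the effective N is 135–192 (power 83–93%) against 120 (78%). The low end is not a floor: as s goes to zero, so does the gain.

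**4. Bias, illustrative only.** Large-sample simulation, 400,000 per arm, 36% control-arm loss. The log-odds of loss rise by 0.7 or 1.5 for each SD fewer work days at T3, with the same three correlations. These mechanisms are assumed.

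- *No true effect, same dependence in both arms:* T4-completer estimate within about 0.003 SD of zero.
- *No true effect, dependence in the control arm only:* completer estimate −0.18 to −0.36 SD, against the intervention.
- *True effect 0.50 SD, same dependence in both arms:* completer estimate 0.40–0.47, because the better-working arm then loses fewer patients.
- *True effect 0.50 SD, control arm only:* completer estimate 0.14–0.33.
- *Estimate using T2 and T3:* within about 0.005 SD of the truth throughout, because loss was made to depend on values that are observed.

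**The case against.** The strongest reply is that this is a matter of missing-data handling, which an article may leave to the analysis plan. Nowhere does the text say that drop-outs are excluded. Multiple imputation could be followed by the stated model unchanged, and inflating 128 to 200 is routine planning that does not define an analysis set. Part of this stands: a reader might infer that the protocol explicitly discards patients without T4, and it does not say so. What remains is that the model it does fix has no place for T2 or T3 data, and its sample size is built on drop-outs adding nothing.

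A reader might also take the year's outcome to be the sum of the T2, T3 and T4 counts. Table 1 gives no recall window, so this is plausible but not shown. If T4 is a report on the whole year, the earlier reports can still serve as predictors of it.

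A third tempting reading is that a T4 comparison is invalid whenever loss relates to work status. That is too strong. With no true effect and equal dependence in both arms there is essentially no bias. The large figures need a link in the control arm only, which nothing in the article documents. Expert support ends at about the time of T3, so it does not clearly explain different loss between months 6 and 12, and the article says that the same data are collected at the same times in both groups.

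**Conclusion.** The point holds as a weakness of the primary model that the article fixes. At 36% loss it forgoes roughly 4 to 13 points of power if between a quarter and all of the drop-outs gave both T2 and T3, and less if fewer did. This rests on the assumed correlations and on ignoring ward clustering. At 40% loss, which the plan itself foresees, the T4-only analysis falls to 120 patients, below the stated 128.

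Bias is a conditional exposure and not a demonstrated error. It is negligible under no effect if loss relates to work equally in both arms, a modest dilution (0.40–0.47 for a true 0.50) if there is an effect, and serious only if the relation differs by arm. The bias figures illustrate assumed mechanisms and do not predict what will happen in this trial.

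The sponsor should change the analysis, because the data are already scheduled. The per-protocol exclusion, which selects patients in the intervention arm only, is a separate problem that this change does not cure.

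**What to change.** Keep the 12-month days-in-work contrast between arms with ward as random effect, and estimate it with all observed T2 and T3 data, in one of two ways:

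- multiply impute the missing T4 outcome separately by arm from the T0, T2 and T3 values, allowing for ward, then fit the stated model; or
- if the reports are interval counts, fit a joint mixed model to the T2, T3 and T4 counts with ward and patient random effects and arm-by-visit terms, and sum the estimates to the year.

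State the recall window of each days-at-work report, since the second route depends on it. Report the T4-completer analysis and a delta-adjusted analysis as sensitivity, the latter because T2 and T3 protect against bias only where loss is explained by observed values.

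The cost is a little more analysis work. No visit, patient or questionnaire is added. The downside is reliance on data being missing at random given what was observed.

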### Aim and research questions

The aim of the planned project is to establish a psychosocial case-management intervention (return-to-work-experts) that supports patients at the interface between inpatient treatment and return to work and to estimate its effects in a cluster-randomized study.

We presume that the intervention (return-to-work-experts, details see methods) will optimize care of the affected patients with regard to improving their return to work, thereby focusing on the interface between in-patient treatment and outpatient care (“occupational discharge management”). The chain of action on the structural and the individual level is visualized in Fig. 1.

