#### Randomization and blinding

We will determine pairs of comparable wards (number of patients, distribution of diagnoses, staff etc.) and then randomize one ward of each pair to the intervention and one ward to the control condition. While the principal investigators will determine the paired wards, the statistical institute of our department (IMedIS) will do the randomization.

Randomization takes place at cluster level (*n* = 14 wards each to the intervention group or control group) to minimize contamination effects [19].

As to the nature of the intervention (implementation of RTW-experts) there will be no blinding.

To avoid selection bias, all patients fulfilling inclusion criteria will be recruited consecutively in the intervention and control group. This process is monitored by the study center and will be reported in form of a CONSORT diagram. There will be special emphasis on documenting how many patients (and for what reasons) did not consent to participate in the trial.

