### Intervention and control condition

The intervention consists of the implementation of Return to Work experts in the participating acute care units. The RTW experts (social workers, who in the framework of the RETURN study are added to existing resources) support patients and mental health care professionals on the wards in all areas related to the possible return of patients to their workplace. The RTW experts will thereby act as case managers, who usually first clarify the specific needs of the clients (i.e. participating patients who might return to an existing workplace), subsequently communicate these needs to all people involved in the treatment process and initiate and accompany a corresponding treatment path. The services of the RTW expert can be claimed by the patients for up to half a year. In order to guarantee a minimum of intervention, it is planned that the RTW experts meet at least twice – one appointment during the inpatient stay and one after release. A maximum of intervention is not defined. Above all, existing support services (e.g. work therapy, cognitive training, socio-educational counseling, etc.) should be activated for the individual patient. However, if there is a limitation of resources, more specific needs or issues (for example, discussions with the patient’s employer, Integration Services, etc.), the RTW expert can also take personal action and support the patients accordingly. In addition, the RTW expert is to be active at the interface between discharge and reintegration and to assist the patient even after discharge in the activation of occupational and outpatient psychiatric-psychotherapeutic support measures. The RTW experts thus assume the function of a job-related discharge management.

The approach of the RTW experts is guideline-based. The RTW experts will be specifically trained. For this purpose, a guideline and a training program for the RTW experts has been established together with the Advisory Board in the first project phase (Kohl et al. in preparation), and will be evaluated within the framework of the study and then revised if necessary, so that the guideline and RTW expert training can be published at the end of the project.

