Staff (and patients) of the control wards will act under “treatment as usual” (TAU) conditions. To avoid contamination bias as far as possible (i.e. staff or patients from control wards getting to know about RETURN), wards were chosen in a way so that there is no overlap in personnel and that there is no regular patient exchange between wards.

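### The primary analysis is per protocol with a two-contact rule that only intervention-ward patients can fail, so the comparison is exposed to selection after allocation and can be biased in either direction

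*Protocol article*

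**What the plan says.** All references are to the protocol article.

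- **Aim.** The section on aim and research questions says that the project will establish the RTW-expert intervention and "to estimate its effects in a cluster-randomized study".
- **Allocation.** Under randomization and blinding, wards are paired, and the plan is to "randomize one ward of each pair to the intervention and one ward to the control condition", 14 wards per condition. Consecutive recruitment in both arms is required so as to avoid selection bias.
- **Primary comparison.** In the section on sample size and statistical analysis: "The primary analysis will be a comparison of days in work at T4 between the intervention and control groups". T4 is 12 months after release.
- **Analysis population.** Same section: "A per protocol approach will be taken to the analysis". The membership rule that follows is that "patients in intervention clusters will be analyzed in this group, if they had contact with the RTW-expert at least once during their inpatient stay". A further contact after discharge is required as well.
- **Origin of the rule.** The two contacts match the planned minimum delivery in the section on intervention and control condition: "one appointment during the inpatient stay and one after release". That section also lets patients claim the service for up to half a year.
- **Control wards.** Staff and patients there "will act under “treatment as usual” (TAU) conditions".

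The text available for review names no intention-to-treat analysis, either as primary or as sensitivity analysis.

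**The concern.** The rule acts in one arm only. Control patients have no RTW expert, so no equivalent filter could be applied to them.

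The rule also acts after allocation. The contact after discharge occurs within the same year in which the outcome accumulates. Whether it happens depends partly on the patient's choice and clinical course, and both are plausibly linked to days in work. Patients who disengage or relapse may miss it, and losing them flatters the intervention. Patients who go back to work quickly may see no need for it, and losing them hides a benefit.

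The rule removes more than patients who never met the expert. Someone seen on the ward but not after discharge fails it too, and this second condition is the one most open to selection.

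What is at stake is the trial's main result. The aim is to estimate the effect of placing RTW experts on wards, in a design whose cluster randomisation the discussion lists as a strength. A contrast between a filtered arm and an unfiltered arm does not estimate that effect, and it undoes after enrolment what consecutive recruitment was meant to protect.

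**Working it through.** **1. The plan's own figure.** A two-sided t-test with standardised difference 0.5, α = 0.05 and 80% power needs 63.8, so 64 per arm and 128 in total. This reproduces the stated number. The planned 200 corresponds to 36% drop-out: 128 / (1 − 0.36) = 200. The sample-size arithmetic is not what fails here.

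**2. Bias under no true effect.** Let f be the share of intervention-ward patients who fail the rule. Let D be the difference in mean days in work, in SD units, between those who pass and those who fail.

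- Mean of the whole arm = (1 − f) × mean(pass) + f × mean(fail).
- Bias = mean(pass) − mean of the whole arm = f × D.

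The document gives neither f nor D, so the values below are assumptions. A negative D gives the same size in the opposite direction. D = 0 gives no bias.

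**3. Type I error.** Take 64 evaluable control patients and 64(1 − f) intervention patients, SD 1, normal approximation. Then SE = √(1/64 + 1/[64(1 − f)]), and the type I error is P(Z > 1.96 − bias/SE) + P(Z < −1.96 − bias/SE).

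| f | D | Bias (SD) | SE | Bias/SE | Type I error |
|---|---|---|---|---|---|
| any | 0 | 0 | – | 0 | 5% |
| 10% | 0.25 | 0.025 | 0.182 | 0.14 | 5.2% |
| 20% | 0.5 | 0.10 | 0.188 | 0.53 | 8.3% |
| 30% | 0.5 | 0.15 | 0.195 | 0.77 | 12.0% |
| 40% | 0.75 | 0.30 | 0.204 | 1.47 | 31% |

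For the two middle rows, the bias is 20% and 30% of the planning effect of 0.5 SD.

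**4. Allowing for wards.** The planned model has a ward random effect, which step 3 ignores. Assume an ICC of 0.05 to 0.10. Mean cluster size is 64/14 = 4.6 in the control arm and 64(1 − f)/14 in the intervention arm. Multiply each arm's variance by 1 + (mean cluster size − 1) × ICC. The type I error becomes 7.9–7.5% (from 8.3%), 11.2–10.5% (from 12.0%) and 28–26% (from 31%). The inflation is smaller but remains.

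**5. A second selection model.** Let a latent tendency to keep contact correlate ρ with days in work, and drop the lowest share q of the intervention arm. The bias is ρφ(c)/(1 − q), where c is the normal quantile of q. With ρ = 0.3, the bias is 0.10 SD at q = 20% (type I error 8.7%) and 0.15 SD at q = 30% (12.1%), close to step 3.

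**6. Power if contact is unrelated to outcome.** With D = 0, the rule only removes patients. At f = 20% and a true effect of 0.5 SD, the plan's t-test has:

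- 30% drop-out: 56 v 70 patients, power 79%
- 36% drop-out: 51 v 64 patients, power 75%
- 40% drop-out: 48 v 60 patients, power 73%

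This treats failing the rule as additional to drop-out. Where the same patients do both, the loss is smaller.

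**7. Price of intention-to-treat.** If 0.5 SD is the effect in the whole allocated arm, 64 per arm gives 80.1% power and no stated figure changes. If it applies only to contacted patients and the others gain nothing, the average effect is 0.5(1 − f): 0.45, 0.40 or 0.35 for f = 10%, 20% or 30%. Power at 64 per arm is then about 72%, 62% or 51% (normal approximation).

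**The case against.** The strongest defence is that the two contacts are the planned minimum of delivery. If the RTW experts achieve it for nearly everyone, f is small and the bias negligible. Nothing in the document points to high failure rates, and the two selection mechanisms could partly cancel. This stands as a limit on size: the upper row of the table is an extreme corner and should not be read as an expectation. It does not rescue the rule, because the plan commits to it whatever the contact rate turns out to be.

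A second defence is that intention-to-treat dilutes the effect. That is true, and step 7 shows that the loss of power can be large. But the diluted effect is the effect of placing experts on wards, which is what the trial set out to estimate.

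Three stronger readings are tempting, and the document does not support them.

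- A reader might infer that the plan is bound to favour the intervention. The direction is not known.
- A reader might infer that the damage cannot be repaired. The data collection section schedules the same measurements in both arms, and the treatment adherence section records contacts, so an intention-to-treat result can be obtained from data already planned.
- A reader might take the wording to mean that patients who fail the rule are moved to the control group. Exclusion is the natural meaning of a per-protocol approach, although the text does not spell it out.

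**Conclusion.** The point holds. The per-protocol choice is stated outright, so it is neither a detail left to an analysis plan nor something lost when the protocol was condensed into an article. It exposes the primary result to one-arm selection after allocation, and it should be changed before the analysis.

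The size is illustrative. At f = 20–30% and D = 0.5 SD, both assumed, the spurious difference is a fifth to almost a third of the planning effect, and the type I error is about 8–12%, or roughly 7.5–11% with an assumed ICC of 0.05–0.10. With few failures, or with contact unrelated to outcome, the type I error stays near 5% and the main cost is power. The case for change rests on the structure of the rule and not on any one of these figures.

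**What to change.** Replace the per-protocol sentence. The primary analysis should be intention-to-treat: every enrolled patient is analysed in the arm to which the ward was randomised, whatever the contact with the RTW expert. Keep the two-contact set as a labelled sensitivity analysis, and state that patients outside it are excluded from that set and not reassigned.

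A complier-average estimate with ward allocation as instrument should be left out, or be exploratory only with its exclusion assumption stated. The RTW experts also support ward staff, so allocation may affect patients who fall short of two contacts.

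**Cost.** A change of wording and no new data collection. With 30–40% expected drop-out, intention-to-treat needs a stated approach to missing outcomes, but the present plan faces the same losses in its control arm. The real downside is dilution if contact rates are low (step 7). The sponsor should therefore say whether the planning effect of 0.5 SD refers to all allocated patients or only to contacted ones, and reconsider power if it is the latter.

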### Acute psychiatric crises, inpatient treatment and return to work

A particularly vulnerable time is that of an acute mental health crisis, which requires inpatient hospital treatment. It tears those affected out of their employment relationships, sometimes over longer periods of time. A successful reintegration of those patients after the acute episode of illness would therefore be an important prognostic factor for the further course of the disease. A failed reintegration in contrast would be a high risk factor for longer incapacity to work, long payment of sickness benefit, unemployment and a less favourable course of the disease.

Present data shows that it is a frequent health (or social) problem. In 2010 about 800,000 psychiatric inpatient cases were documented in Germany [13]. About 20% (= 160,000 people) of these cases were working patients [14]. Up to 30% of these patients did not return to work after discharge from hospital [14] and of those returning it was unclear how long they were able to successfully resume their employment relationships. Considering the related social decline and associated reduction in participation in social life, these numbers are alarming [15, 16].

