**Fig. 1 Fig1:**
[figure not shown]
German terms and their translation: BEM = Betriebliches Eingliederungsmanagement (Corporate integration management), Stufenweise Wiedereingliederung (gradual reintegration)

We expect improvements in the number of patients who will be able to return to work and also in the number of days at work in the year after release from hospital. This could also result in substantial economic savings (for example, sickness benefit, loss of productivity, etc.). Mediators of these expected improvements are increased numbers of patients for whom specific supportive measures (e.g., work therapy, gradual reintegration, BEM processes, etc.) are initiated. We assume that the proposed intervention primarily will increase the implementation of measures already existing in routine care and will help to overcome the interface problem at the time of inpatient discharge.

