### Data collection

The same data at the same time points will be collected in the intervention and control group (Table 1). Data collection will take place at five times during the inpatient stay and after discharge.

**Table 1 Tab1:** Planned data collection

	T0 (shortly after admission to hospital)	T1 (shortly before release from hospital)	T2 (3 months after release)	T3 (6months after release)	T4 (12 months after release)
Patient					
Demographics including information on					
School and vocational training	x				
Employment relationsship	x				
Business, enterprise (industry)	x				
Business, enterprise (size)	x				
Motivation	x	x	x	x	x
Anxiety, confidence	x	x			
Days of incapacity to work	x		x	x	x
COPSOQ	x			x	
COPSOQ (additional information)	x				
Self-stigma of mental illness scale short form – self-concurrence	x	x		x	
Cognitive appraisal of stigma-related stress	x	x		x	
Questions concerning disclosure of the disease at the workplace including					
Questions on the decision-making phase	x	x		x	
Questions on the decision to disclose	x	x		x	
Questions on the attitude towards disclosure	x	x		x	
Decisional Conflict scale	x	x		x	
Cognitive performance level		x			
CSSRI	x	x	x	x	x
Preparation of the return through the hospital		x			
Preparation of the return through the employer		x			
Preparation of the return through the RTW expert (intervention group only)		x		x	
Questions on the existing help network		x		x	x
Content of the employer support				x	
Evaluation of the employer support				x	
Evaluation of the RTW expert support (intervention group only)				x	
EuroQOL - Gesundheitsbarometer	x	x		x	
EQ-5D		x		x	x
Self-efficacy expectation (RTW-SE)		x			
Resilience (RS-13)					x
Patient Health Questionnaire (PHQ-D)		x			
Days at work			x	x	x
Days of incapacity for work			x	x	x
Days of partial return to work			x	x	x
Questions on discrimination at the workplace				x	
Coping				x	
Attending physician					
CGI	x	x			x
GAF	x	x			x
ICD Diagnosis and medical history	x	x			x
HoNOS		x			
Prediction on return to work		x			
RTW expert (intervention group only)					
Type and scope of workplace-related support		x		x	
Evaluation of workplace-related support		x		x	
Prediction on return to work		x			
Quality of relationship		x		x	
Return to work				x	
Questions concerning the use of communication media				x	
Open summary				x	

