#### Secondary outcomes

As outlined above an improved return to work following an in-patient psychiatric care treatment of patients may also result in a shorter period of **time to return to work** (partial/full), lower **termination rates** (both sides), a higher **quality of life** (EQ-5D, [20]), a higher **social functional level** (Mini-ICF-APP, [21]; Global Assessment of Functioning (GAF), [22]), a higher **job satisfaction** (German version of the Copenhagen psychosocial questionnaire (COPSOQ), [23]), a different **perception of stigmatization** (Self-stigma of mental illness scale – short form – subscale self-concurrence, [24]; Cognitive appraisal of stigma-related stress, [25]), lower **decisional conflict in regard to disclosure of the mental illness** (Decisional conflict Scale, [26]) and probable reduced **relapse rates**.

The basis for estimating the **cost of the illness** and the **health economic evaluation** of the RTW intervention are the medical and psychosocial health services made use of by the subjects and the number of days of incapacity for work for the whole study period.

The days of incapacity to work of the patients are on the one hand directly requested by the patients and their practitioners. It is envisaged that the patient’s details will be checked against those of some health insurance companies in order to assess the extent to which the data match.

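### Time to return to work is a listed secondary outcome, but the models given for secondary outcomes (linear or GEE logistic) cannot handle patients with no observed return time

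*Protocol article*

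**What the plan says.** The Secondary outcomes section of the protocol article opens its list with "a shorter period of time to return to work (partial/full"). The section on sample size and statistical analysis then assigns models by type of outcome. For continuous outcomes it says "Random effect linear models will be fitted to the continuous secondary outcome measures, analogous to the primary analysis". For binary outcomes it says "For binary secondary outcome measures, logistic regression models using GEEs will be fitted". No other model class is given for the clinical secondary outcomes, and the text has no censoring rule and no value for a patient who has not returned by 12 months. The same section labels this work exploratory: "Exploratory analyses will be performed to assess the effect of the intervention on the secondary outcome measures".

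Three other statements bear on how many patients will have no return time:

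- The background section on acute crises and return to work says "Up to 30% of these patients did not return to work after discharge from hospital".
- The sample size paragraph expects 30-40% drop-out.
- The text under Fig. 1 says "We expect improvements in the number of patients who will be able to return to work".

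Table 1 collects days at work, days of incapacity and days of partial return from patients in both arms at 3, 6 and 12 months after discharge.

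**The concern.** Time to return is an event time. It is observed only for patients who return while under follow-up. It is not binary, and the abstract lists the return rate as an evaluation of its own, so a yes/no analysis would not replace it. Of the two classes offered, the linear model is the one it falls under.

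A linear model needs a number for every patient it includes. If it is fitted to patients with an observed time, it compares subsets formed after randomisation, and the plan itself expects the intervention to change who is in them. Patients who return because of the intervention may well return late, and adding them raises the intervention mean even when nobody is slowed. If non-returners are instead assigned a value such as 365 days, they stay in the analysis, but the value is a convention, and patients lost to follow-up before returning still have no defined value. At stake is a secondary result that readers will look at closely, because it describes what the intervention is meant to do.

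**Working it through.** **The plan's own figure.** The article gives no figure for time to return. Its only sample size figure is 128 in total, for a t-test with effect size 0.5, 80% power and two-sided 5%. The exact t-test calculation gives 63.77, hence 64 per arm and 128 in total, so that figure reproduces. It does not bear on this outcome.

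**Inputs from the article.** 100 patients per arm, follow-up of 12 months (365 days), up to 30% not returning, 30-40% drop-out, and a higher number returning expected on intervention. If the background figure applied to controls, up to 0.30 × 100 = 30 of them would have no return time even without drop-out. The article does not say how far non-return and drop-out overlap, so the two are not added here.

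**Inputs assumed (not in the article).** On control, 70% return at a mean of 90 days. On intervention, the same 70% return at a mean of m days, and an extra share e returns late at a mean of L days. The intervention is then no worse for anyone.

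**Formulas.**

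- Returners only, intervention minus control: (0.7m + eL)/(0.7 + e) − 90.
- Non-returners set to 365: [0.7m + eL + (0.3 − e) × 365] − [0.7 × 90 + 0.3 × 365].
- The returners-only sign is wrong when e(L − 90) > 0.7(90 − m).

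**One worked case (m = 85, e = 0.10, L = 250).**

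- Returners only: (59.5 + 25)/0.8 − 90 = 105.6 − 90 = +15.6 days, seemingly slower.
- Non-returners at 365: (59.5 + 25 + 73) − (63 + 109.5) = 157.5 − 172.5 = −15.0 days, faster.

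**Threshold.** With m = 81 and L = 250, reversal needs e > 0.7 × 9/160 = 0.039, about 4% extra late returners.

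**Range.** Over m = 80, 85, 90; e = 0.05, 0.10, 0.15; and L = 200, 250, 300 (27 combinations), the returners-only difference runs from −2.0 to +37.1 days and has the wrong sign in 26. With non-returners at 365 it runs from −31.8 to −3.2 days and is always in the right direction.

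**Simulation** (100 per arm, 365 days, 500 runs, no ward effect, no drop-out, m = 81, L about 250):

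| Extra late returners | Returners-only difference (days) | Wrong sign | Non-returners at 365 (days) | Wrong sign | Mean Cox HR for return | HR below 1 |
|---|---|---|---|---|---|---|
| 0% | −8.7 | 18% | −5.6 | 37% | 1.06 | 37% |
| 5% | +2.4 | 57% | −9.7 | 29% | 1.12 | 26% |
| 10% | +11.0 | 81% | −19.1 | 18% | 1.25 | 13% |
| 15% | +20.5 | 96% | −22.4 | 14% | 1.33 | 6% |

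As more patients return, the returners-only comparison is wrong more often, while the other two are wrong less often.

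**The case against.** The strongest reply is that the article never says which class time to return belongs to, and never says that non-returners are left out. It is a condensed account, and a survival method for one exploratory outcome could stand in an analysis plan that is not shown. This is fair as far as it goes, but the article does assign models to secondary outcomes, and neither class fits this one. Followed as written, the text leads to a linear model.

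A second reply is that the linear model need not mislead. With non-returners set to 365 days and no drop-out, it gives the difference in restricted mean time over the year, a sound measure. This stands. It fails only once patients are lost before returning, and the plan expects substantial drop-out.

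A third is that the reversal depends on assumed timings. This also stands: with no extra returners, the returners-only comparison points the right way on average.

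Three stronger readings are tempting and are not supported:

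- **That the plan will report the wrong direction.** This needs a returners-only fit, which the article does not state, and late extra returners, for which it gives no data.
- **That return would be measured differently in the two arms** because Table 1 has a return-to-work item completed by the RTW expert in the intervention arm only. That item is scheduled at 6 months only, nothing makes it the source of this outcome, and patient work-day items are collected in both arms at all three follow-ups.
- **That 30% never return and a further 30-40% drop out.** The 30% is a background upper figure for working inpatients after discharge, not a trial estimate, and the two groups may overlap.

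**Conclusion.** The point holds as a mismatch between a listed outcome and the models provided. Time to return to work will be unobserved for a sizeable share of patients, the plan expects the number returning to differ by arm, and the stated models give no valid way to include those without a return time. Dropping them can bias the estimate. Under the assumed timings the bias ranges from making a benefit look smaller to reversing it by up to 37 days, and about 4% extra late returners is enough for reversal in the scenario with m = 81 and L = 250. Assigning 365 days avoids the reversal in every scenario examined but leaves drop-outs unresolved. The sizes rest on assumed return times and ignore ward effects and drop-out. The primary comparison of days in work is not affected, and the outcome is exploratory, so this should be corrected but does not threaten the trial's main conclusion.

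**What to change.** State that time from discharge to first partial return and time from discharge to first full return are analysed separately, each with a time-to-event model that accounts for ward, for example a Cox model with ward frailty or ward-robust variance. Keep patients who have not returned in the analysis, censored at 12 months, and censor drop-outs at last contact. Use patient-reported data from the 3-, 6- and 12-month assessments in both arms. Cumulative incidence curves with job loss as a competing event would be a useful addition but are optional.

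The cost is a few sentences of analysis wording. The Table 1 items are numbers of days, so one question on the date of return may have to be added if dates cannot be derived from them. Censoring at drop-out assumes that loss is unrelated to the chance of returning. With 30-40% loss expected, that assumption should be stated and its effect on the result examined.
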